### Behaviour change techniques

Self-regulatory BCTs are provided for the H + BCTs and the LM + BCTs groups. These are strategies to facilitate adherence to the high and low-to-moderate intensity exercise programs, respectively. These support strategies focus on the adherence to the exercise intervention, primarily on the endurance exercise, as it is home-based, and on maintaining exercise according to individual preferences after the completion of the interventions. The BCTs include a) *behavioural goal-setting*, b) short-term *action planning*, c) *self-monitoring,* d) *review of behaviour goals,* e) *problem solving* and *functional behaviour analysis* to identify affect individual-specific determinants of exercise behaviour, and f) long-term *coping planning* to maintain physical exercise by own choice after the intervention is completed. In addition, motivational aspects are explored by initial interviews based on a) previous experiences with physical exercise, b) persons’ outcome expectations for following the exercise intervention as prescribed, c) persons’ anticipated barriers and facilitators following the exercise intervention, and d) self-efficacy to partake in planned weekly exercise. The BCTs are provided according to protocol, but are individually tailored according to each participant’s need and functional behavioural analyses. Each participant meets their coach on a regular basis during the program, with gradually decreasing frequency in order to enhance self-regulation at the end of the intervention. These coaching sessions take place either in connection with the scheduled exercise sessions or via phone. Participants with access to internet can use electronic and easily accessible self-monitoring of exercise behaviour in a web portal developed for the Phys-Can study (described below).

### Education of coaches

Coaches (physiotherapists and personal trainers) have been trained to provide the interventions in the four groups. The education consisted of three common course days for all coaches and three additional days for those providing the BCT conditions with home assignments between course days. The education included lectures and seminars on cancer and cancer treatment, exercise physiology, and repeated practice sessions in the gym according to the intervention protocol on high and low/moderate exercise. Additional lectures and practice on exploration of motivation and use of BCTs were given to coaches providing the BCT conditions.

Written intervention protocols have been developed, specifying all intervention components in the four groups. The coaches are to follow the protocol closely, keep logs of attendance at gym sessions, check heart rate during endurance sessions and monitor any adverse advents related to exercise. Adverse events caused by the exercise are registered in a web-portal (described below). Grade 1 (e.g. muscle strain) means that the participant have to terminate the ongoing specific exercise but can continue with the exercise session. Grade 2 (e.g. fall in blood pressure) means that the participant must terminate the exercise session. Any severe adverse events (e.g. fracture) are reported directly to the PI and managed by healthcare.

To address the coaches’ fidelity to the intervention protocol, research staff visit the gyms repeatedly during the intervention, giving feedback on both physical exercise and use of BCTs. Regular project group meetings are held with all project personnel, where issues about delivering the intervention are discussed and solved. In addition, one coach representative from each study site takes part in monthly Skype meetings where common issues relating to the intervention are discussed and coordinated. Coaches’ use of BCTs is monitored by audio recordings of conversations between coaches and participants, and individual feedback is given by one of the research staff.

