**Fig. 1 Fig1:**
[figure not shown]
Diagram of the participant flow through enrolment, baseline measurement, randomization, and follow-up. H = high intensity training; L = low intensity training; BCT = Behaviour Change Technique

The RCT is stratified and within each stratum randomization is carried out following a permuted block design with 8 participants per block. The defined strata are the three hospitals (Linköping, Lund and Uppsala) and three cancer sites yielding 9 strata. When all baseline measurements are finalized and reported in the project’s electronic case report form, the randomization is generated automatically in a web-portal (described below) of participants to an exercise group according to predefined strata (see above). The personnel in charge of recruitment then contact the participant with information on study condition and the first visit to the gym is scheduled.

All participants will exercise at least twice weekly for a period of 6 months under the guidance of trained coaches. Training intensity is 40–50% (LM) or 80–90% (H) of each individual’s heart rate reserve (Heart rate reserve = HRpeak-HRrest) and maximal muscle strength.

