### Sample size

The calculated sample size was based on detecting the main factorial effects of each factor on Multidimensional Fatigue Inventory (MFI) Physical Fatigue (PF) after completed intervention [32–34]. The target main effect size was determined to be 2, which according to Purcell et al. [35] is the minimal clinically important difference for the MFI-PF. We assumed that the standard deviation (SD) of PF was 5 in all four treatment arms, which is the SD reported in Purcell et al. [35], Hagelin et al. [36] and in an ongoing study within our research group (manuscript in preparation). Because three tests (two main and one interaction effect) were planned, the 5% significance level was adjusted using Bonferroni correction. In order to have 80% power to detect a main factorial effect of 2 under the null hypothesis of no effect, 67 individuals in each of the four treatment arms are needed, with a total sample size of 268 individuals.

Further adjustments of the sample size were necessary for several reasons. First, the sample size calculation was based on the assumption of no interaction effects. However, Montgomery et al. [29] argue that, if anticipating quantitative interactions, the trial should be powered to detect those effects. Interaction effects often are much smaller in size compared to the main effects. In clinical trials, it is therefore rare to have 80% power to detect the interaction effect. For instance, given the calculated sample size in the present study, the trial would have a power of only 22% to detect an interaction effect of 1. However, in the present study a possible interaction between the factors is of clinical interest. Thus, the original sample size was doubled, increasing the power to detect the interaction between to approximately 50%. Second, to account for missing data and drop-outs, the original sample size was increased further by 30%. Third, given that we include a baseline assessment, and assuming a moderate correlation (0.3) between the MFI-PF at baseline and follow-up assessments, the sample size can be reduced by approximately 10% [37]. Combining the above, we concluded that including approximately 150 individuals in each treatment arm, 600 individuals in total, should meet the statistical requirements of the trial.

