### Statistical analysis

The data will be analysed according to the intention-to-treat (ITT) principle, i.e. all participants will be analyzed as randomized, regardless of whether they complete the intervention as planned. The primary parameters of interests are the three factorial effects (2 main and one interaction) after completed intervention. Each factorial effect will be estimated taking into account the stratified design following Imbens and Rubin [53]. Thus, we will provide estimates for the overall factorial effects, which are the primary parameters of interest, and also stratum-specific factorial effects which could facilitate external validity. Baseline measurements will be included in the analysis model to increase the precision of the estimates.

Drop-outs and missing values will be handled according to the following procedure. The main analysis will be based on data where missingness is handled using multiple imputations by chained equations. The specification of the multiple imputation model (e.g. choice of auxiliary variables) will be decided after comparing the subject characteristics in those with complete and incomplete data. Under the assumption of missing at random (MAR), an analysis based on multiple imputation conforms with the ITT. Due to the assumption of MAR, which could be a strong assumption to make, factorial effects will also be estimated using complete blocks only. This is a result from the permuted block design which allows for unbiased estimation of the factorial effects using the complete blocks only. Sensitivity analysis will conducted by comparing estimates from the two analyses above with estimates based on complete cases only, a pattern-mixture model, and tipping points analyses [54].

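### Coaches appear to be partly nested within the BCT factor, and the stated sample size and estimator make no allowance for coach clustering in the BCT main effect

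*Protocol article*

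**What the plan says.** Education of coaches states that "Coaches (physiotherapists and personal trainers) have been trained to provide the interventions in the four groups". All coaches shared three course days, and there were "three additional days for those providing the BCT conditions". It adds that "Additional lectures and practice on exploration of motivation and use of BCTs were given to coaches providing the BCT conditions".

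Contact with coaches is sustained. The Design section (text under Fig. 1) says "All participants will exercise at least twice weekly for a period of 6 months under the guidance of trained coaches". In the section on behaviour change techniques, "Each participant meets their coach on a regular basis during the program".

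Randomisation is by individual, in permuted blocks of 8 within strata: "The defined strata are the three hospitals (Linköping, Lund and Uppsala) and three cancer sites yielding 9 strata". Coach is not a stratum.

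Statistical analysis makes the two main effects and the interaction the primary parameters, and says "Each factorial effect will be estimated taking into account the stratified design". Baseline measurements enter the model. Under Sample size, "We assumed that the standard deviation (SD) of PF was 5 in all four treatment arms", with a target main effect of 2, a Bonferroni correction for three tests and 80% power. This gives 67 per arm (268 in total), later raised to about 600. Neither section mentions coach, clustering or an ICC.

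**The concern.** Individual randomisation makes participants exchangeable at entry. Six months of coached exercise can then make the outcomes of people who share a coach more alike. When each coach works at only one level of a factor, differences between coaches add to the variance of that factor's effect, and a formula that assumes independence leaves this component out.

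The training scheme ties coaches to the BCT factor. Adjusting for hospital does not remove the problem, because it lies between coaches within a hospital, and those are the differences that line up with BCT.

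At stake is the BCT main effect. Its interval would be too narrow, its test would exceed the Bonferroni level, and chance differences between two sets of coaches could be read as an effect of BCTs.

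**Working it through.** **1. Reproduce the plan's figure.** Inputs from Sample size: effect 2, SD 5, power 80%, three tests. Two-sided testing is assumed, so alpha = 0.05/3 = 0.0167 and z = 2.394.

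n per factor level = 2(2.394 + 0.842)² × 5²/2² ≈ 131, or 66 per arm. The noncentral t version gives 67 per arm (power 0.806 at 67, 0.799 at 66), which matches 67 and 268. For an interaction effect of 1 with 134 per level, power is 0.2246, against the stated 22%. These formulas assume independent participants, so the plan's figures follow with no allowance for clustering.

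**2. BCT main effect if coaches are nested in BCT level.** The number of participants per coach (m) and the ICC are assumptions.

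Design effect DE = 1 + (m − 1) × ICC. True error = 2[1 − Φ(2.394/√DE)].

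| m | ICC 0.01 | ICC 0.02 | ICC 0.05 |
|---|---|---|---|
| 10 | DE 1.09, 2.2% | DE 1.18, 2.8% | DE 1.45, 4.7% |
| 20 | DE 1.19, 2.8% | DE 1.38, 4.2% | DE 1.95, 8.7% |
| 30 | DE 1.29, 3.5% | DE 1.58, 5.7% | DE 2.45, 12.6% |

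Example for m = 20, ICC 0.05: √1.95 = 1.40 and 2.394/1.40 = 1.71, giving a two-sided error of 8.7%. With N = 600 the independence standard error is 5 × √(4/600) = 0.41 points; the true one is 0.41 × 1.40 = 0.57.

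**3. Clustering only in the BCT arms.** The wording about a participant's own coach appears only in the BCT section, so non-BCT participants may not keep one coach. The design effect for the contrast is then the average of the clustered and unclustered halves, again with m = 20.

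- ICC 0.02: (1.38 + 1)/2 = 1.19, true error 2.8%.
- ICC 0.05: (1.95 + 1)/2 = 1.475, true error 4.9%.

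**4. Which effects are hit.** A simulation used N = 600, SD 5, normal coach intercepts, about 20 participants per coach and 6,000 runs. Cells show true SE divided by independence SE at ICC 0.02 / 0.05.

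| Coach allocation | BCT | Interaction | Intensity |
|---|---|---|---|
| Nested in BCT level, both intensities | 1.18 / 1.38 | 0.98 / 0.98 | 0.99 / 0.97 |
| Specific to one of the four arms | 1.20 / 1.43 | 1.20 / 1.44 | 1.19 / 1.42 |
| Working across all four arms | 0.99 / 0.95 | 0.99 / 0.98 | 1.00 / 0.98 |

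In the first row the simulated error of the BCT test is 4.6% / 8.6%, in line with step 2. A coach who works at both intensities adds the same intercept to both, so it cancels from the interaction and from the intensity effect.

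**5. Power for a BCT effect of 2.** With m = 20 analysed per coach and ICC 0.05, power falls from 0.994 to 0.867 at N = 600. With 30% lost (600 × 0.7 = 420) it falls from 0.956 to 0.706.

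**The case against.** **Nesting is partly inferred.** The article says coaches as a body cover the four groups and that some had extra training. It does not say that BCT-trained coaches worked only in BCT arms. If they also served non-BCT participants, the understatement shrinks, and with full crossing it disappears. This stands and makes the point conditional. Full crossing, however, would need every coach to have had the extra days, and the article distinguishes those who did.

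**Delivery is standardised.** Written protocols, gym visits, audio recordings and feedback should lower the ICC. That is fair, but they do not make it zero.

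**A condensed article may leave a coach term to a fuller document.** It may, and the coach may already be identifiable from the attendance logs that coaches keep. The article does, however, describe its estimator and a power calculation in some detail, and neither allows for coach.

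**Stronger readings to avoid.** A reader might infer that the interaction's standard error is also too small. If coaches are nested in BCT level but work at both intensities, it is about right (ratio 0.98). Only arm-specific coaches, or coach effects that differ by intensity, would disturb it, and arm-specific coaches would disturb the intensity effect as much. A reader might also infer that the 80% power is lost. That figure belongs to 268 participants, not to the planned 600, where there is slack.

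**Conclusion.** The point holds for the BCT main effect, conditionally. The training scheme indicates that coaches are at least partly nested within BCT, and the stated sample size and estimator allow only for strata and baseline. If the coach ICC is above zero and coaches do not work across BCT levels, the standard error of that effect will be too small, and the strata will not repair it.

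The size rests on assumed coach numbers and ICC. At 20 participants per coach and ICC 0.01 to 0.05, the true error is about 2.8% to 8.7% against a nominal 1.67%. It is smaller if only the BCT arms are clustered, or if BCT-trained coaches also serve the other arms. The article does not establish that the standard errors are too small in fact, or by how much. At the planned size the main consequence is for interval width and type I error; power matters more if 30% are lost and the ICC is near 0.05.

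**What to change.** - State how coaches are allocated: whether BCT-trained coaches also serve non-BCT participants, whether coaches work at both intensities, and whether non-BCT participants keep one coach.
- Record each participant's assigned coach, and analyse by assigned coach.
- Estimate the BCT main effect with a random coach effect, or with coach-clustered standard errors and a small-sample correction. Keep the adjustment for strata and baseline.
- Extend this to the interaction and intensity effects if coaches prove to be arm-specific.
- Report the estimated ICC, and state that the sample-size calculation assumes no coach clustering.

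The cost is one data field, if the coach is not already recorded, and one model term. The downside is a wider interval for the BCT effect.

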### Endurance exercise

The first six weeks after inclusion the participants familiarize themselves with the use of the heart rate monitor and perceived exertion using the Borg-scale [40] for monitoring of exercise intensity and perceived exertion. Four endurance sessions are conducted at the gym and supervised by a coach. Thereafter, the endurance exercise is home-based and followed up by a coach. All participants are instructed to warm-up for approximately 10 min at moderate intensity before each endurance session. The participants are instructed to wear the heart rate monitor during every session and report perceived exertion in a diary. Exercise frequency is recommended to be 2–4 times a week. The low-to-moderate intensity group do continuous-based exercise (running, cycling, walking uphill or any other endurance-based activity) in bouts of at least 10 min at an exercise intensity of 40–50% of the heart rate reserve. The main aim is to reach 150 min of moderate intensity per week. The high intensity group conduct high-intensity interval exercise at an exercise intensity of 80–90% of the heart rate reserve (at the end of the 3rd session) with two minutes exercise (running, cycling, walking uphill or any other endurance-based activity) and two minutes rest between sessions. The participants start with five sessions, increasing to six after the six weeks familiarization period, thereafter adding one session every fourth week until 10 sessions are reached as the maximum, corresponding to 75 min of vigorous intensity per week.

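### The exercise adverse-event register admits events by presumed cause and is monitored by unblinded coaches, so a comparison of exercise harms by intensity that uses it is open to bias and under-ascertainment

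*Protocol article*

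**What the plan says.** All of the following is in the protocol article.

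- *Education of coaches*: the coaches' duties are to keep attendance logs, "check heart rate during endurance sessions and monitor any adverse advents related to exercise". The next sentence gives the recording rule: "Adverse events caused by the exercise are registered in a web-portal". It is in the passive and does not say who attributes or enters an event.
- Same section, grading: Grade 1 "means that the participant have to terminate the ongoing specific exercise but can continue with the exercise session"; Grade 2 "means that the participant must terminate the exercise session". Severe events have their own route: "Any severe adverse events (e.g. fracture) are reported directly to the PI and managed by healthcare".
- Same section, on the coaches: they "have been trained to provide the interventions in the four groups".
- *Resistance training*: two supervised gym sessions a week.
- *Endurance exercise*: two to four sessions a week are recommended and four in total are supervised at the gym. "Thereafter, the endurance exercise is home-based and followed up by a coach". Participants wear a heart rate monitor and note perceived exertion in a diary.
- *Secondary outcome measures*: toxicity and adverse events graded by NCI-CTC 4.0 are taken from quality registers and case records. No exercise-causality condition is attached, and coaches are not the source.
- *Background*, objectives: the adverse-effect comparison named between the two intensities concerns oncological adverse effects.

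**The concern.** Whether an event was caused by exercise is a judgement. Here that judgement is made before recording rather than after. If the same dizzy spell is more readily put down to exercise in one intensity arm than in the other, the register will show a difference that the events themselves do not, or will hide one that they do. Events left out at entry are not kept in that register and cannot be reclassified at analysis.

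Two features add to this. The people named as monitors know the intensity, because they deliver it. The grade definitions also need an exercise or session to have been stopped, so a complaint that appears after the session fits neither grade, and much of the training takes place with no coach present.

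The stake is what the trial can say about harm from the exercise itself. The *Discussion* intends the results to inform practice on high versus low-to-moderate intensity, and a reader will want the minor exercise harms of each beside the fatigue result.

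**Working it through.** The article gives no figure on this point to reproduce. The check sets the sections side by side and then counts sessions.

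**1. What each route captures**

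- *Exercise register (Education of coaches).* Entry condition: attributed to exercise. Monitor: the coach. Grades: tied to stopping an exercise or a session.
- *Severe events (same section).* They go straight to the principal investigator and to healthcare.
- *Clinical data (Secondary outcome measures).* Entry condition: the event appears in a register or case record. Independent of coaches and of exercise attribution.

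An event that is not severe, is not presented to a clinic, and is either not attributed to exercise or not brought to a coach's notice meets none of the three conditions. Minor strains, falls and dizziness at home are the obvious candidates. The diary does not clearly fill the gap, since the article describes it as holding perceived exertion.

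**2. Share of training without a coach present**

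Inputs: resistance 2 sessions per week, all supervised; endurance 2 to 4 per week, of which 4 in total are supervised; duration 6 months, taken as 24 to 26 weeks (an assumption, since the article gives months only).

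Formulas, with W weeks and f endurance sessions per week:

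- total sessions = 2W + fW
- home sessions = fW − 4
- home share = (fW − 4) / (2W + fW)

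Results:

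- W = 24, f = 2: (48 − 4) / (48 + 48) = 44/96 = 46%
- W = 24, f = 4: (96 − 4) / (48 + 96) = 92/144 = 64%
- W = 26, f = 2: (52 − 4) / (52 + 52) = 48/104 = 46%
- W = 26, f = 4: (104 − 4) / (52 + 104) = 100/156 = 64%

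The range hardly depends on the assumed weeks. A coach is present at about 36% to 54% of all sessions, but at only 4 of 48 to 104 endurance sessions, that is 3.8% (4/104) to 8.3% (4/48).

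**3. What the count does and does not show**

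It measures how much training is unobserved, not bias. The recommended endurance frequency is the same for both intensities, so by plan the unobserved share does not differ by arm. It bears on under-ascertainment. Attribution bias comes from the entry condition combined with unblinded monitoring, and the article contains nothing from which its size could be computed.

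**The case against.** The strongest reply is that this register is not the trial's adverse-event source. The objective names oncological adverse effects, which the clinical records serve. The register is described among the coaches' duties, and the *Statistical analysis* section assigns it no comparison between arms. This stands: a reader might infer that the trial as a whole records only exercise-caused events, and that is wrong. The point is confined to the exercise register and to any comparison that draws on it.

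Further replies, and what remains of each:

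- *Coaches are not said to judge causality.* Correct. A reader might infer it because monitoring and registration are in adjacent sentences, but the article names no one. The entry condition applies whoever decides, and no masked judgement is described.
- *The grades are not limited to the gym.* Correct. Neither definition names a place, and a session can be stopped at home. What remains is that they rest on stopping, and that at home a coach does not see it.
- *Coach absence is softened.* Also correct. Home training is followed up, two supervised sessions a week give regular contact, and severe events go elsewhere. This reduces loss but does not undo the filter on cause.
- *This is a condensed article.* Questions put to participants and causality procedures may well be in the written intervention protocols, and their absence here is not the complaint. The complaint is the recording rule that the article does state.

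**Conclusion.** The point holds for the exercise register. As stated, it takes in events by presumed cause, under monitors who cannot be blind to intensity, with grades that rest on stopping. Between 46% and 64% of planned sessions, on 24 to 26 weeks and two to four endurance sessions a week, have no coach present. Minor events that never reach a clinic can miss both this register and the clinical records. A comparison of exercise-related harms by intensity that uses the register is therefore open to attribution bias and under-ascertainment, of unknown size and direction.

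A reader might go further and say that the trial's safety comparison is biased and incomplete. The article does not support that. It shows a risk and not a result, and the stated oncological adverse-effect objective has its own source. The primary fatigue analysis is not touched. The change is worth making because it is cheap and because events filtered out at entry are not held in the register for later analysis.

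**What to change.** 1. In the portal, register every adverse event that occurs during an exercise session or within a fixed window after it, whatever its suspected cause. State the window in advance.
2. Elicit events with one standard question, identical in all four arms, at existing coach contacts or in the diary or portal, and have it cover home sessions explicitly. Identical wording matters for the second factor too, because the regular coaching meetings are described within the behaviour change component and could otherwise give those arms more occasions to report.
3. Record relation to exercise as a separate field and not as a condition of entry.
4. Report all events by randomised intensity as the main comparison of harms from this register. Show related events as a subset, read with caution because a separate field does not make the attribution blind.

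The handling of events and the existing grades as instructions to coaches need not change; this concerns recording only.

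Cost: one portal field and one question at contacts that already take place. The downside is more low-grade events to enter. Events filtered out before the change may not be recoverable, so the report should give the date on which the rule changed.
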